## Abstract

**Background:**

The one year prevalence of thoracic back pain has been estimated as 17% compared to 64% for neck pain and 67% for low back pain. At present only one randomised controlled trial has been performed assessing the efficacy of spinal manipulative therapy (SMT) for thoracic spine pain. In addition no high quality trials have been performed to test the efficacy and effectiveness of Graston Technique^® ^(GT), a soft tissue massage therapy using hand-held stainless steel instruments. The objective of this trial is to determine the efficacy of SMT and GT compared to a placebo for the treatment of non specific thoracic spine pain.

**Methods:**

Eighty four eligible people with non specific thoracic pain mid back pain of six weeks or more will be randomised to one of three groups, either SMT, GT, or a placebo (de-tuned ultrasound). Each group will receive up to 10 supervised treatment sessions at the Murdoch University Chiropractic student clinic over a 4-week period. Treatment outcomes will be measured at baseline, one week after their first treatment, upon completion of the 4-week intervention period and at three, six and twelve months post randomisation. Outcome measures will include the Oswestry Back Pain Disability Index and the Visual Analogue Scale (VAS). Intention to treat analysis will be utilised in the statistical analysis of any group treatment effects.

**Trial Registration:**

This trial was registered with the Australia and New Zealand Clinical Trials Registry on the 7^th ^February 2008. Trial number: ACTRN12608000070336

## Background

Published studies of the epidemiology of non-specific thoracic pain are uncommon. Niemelainen found that the one year prevalence of mid back pain in Finnish men was 17%, compared to 64% with neck pain and 66.8% who reported low back pain [1]. When upper or mid back pain was present, disability tended to occur less than if the pain was reported in the neck or low back. However, when disability was reported, the number of days of disability was similar when the pain involved the upper or mid back compared to other regions.

Commonly used treatment options for non specific thoracic spine pain include massage, mobilisation, manipulation, acupuncture, and other physical therapies such as heat, electro-therapies, ultrasound and also non steroidal anti-inflammatories. A search of the literature concerning thoracic spinal pain established that there are no high quality studies for any of these modalities. There are some individual studies, however none show unequivocal proof of efficacy or effectiveness.

To date we are only aware of one published randomised controlled trial performed assessing the effectiveness of spinal manipulative therapy on thoracic spinal pain [1]. Spinal manipulative therapy (SMT) was compared to a placebo group receiving non functional ultrasound in a small trial consisting of 30 patients with "mechanical" thoracic spine pain. The authors reported mixed results. The SMT group demonstrated significantly better reductions in numerical pain ratings and improvements in lateral flexion at the end of a two to three week treatment period. These findings were maintained at one month follow up, however at this point they were no longer statistically significant. Concurrently there were no significant differences between groups in McGill Pain Questionnaires and Oswestry Pain Disability Indices at any point of the trial. Limitations such as a small sample size and inadequate follow up were acknowledged by the author. This, in combination with a lack of trials undertaken in this area, provides further evidence that future trials are warranted in determining the efficacy of SMT for the treatment of non specific thoracic pain.

For the purposes of this study we have chosen to review the following modalities; spinal manipulative therapy and Graston technique^® ^(GT). The reasons for these choices are that spinal manipulation is a very common treatment worldwide and GT is a popular massage technique in the United States and becoming more popular in other developed countries. In addition, GT is taught and used routinely at the Murdoch University Chiropractic Clinic.

Soft tissue or massage therapy is described by Walker et al as a very popular method for the treatment of low back pain in a general population [2]. At present, research has been undertaken to assess the effects of massage therapy on pain, function and patient satisfaction in adults with mechanical neck and low back pain [3]. However, no evidence exists for this same modality in the treatment of non specific thoracic pain.

Graston Technique^® ^is a massage system revolving around several hand-held stainless steel instruments. The promoters of the Graston Technique [4] claim that the instruments are much like tuning forks as they reportedly resonate in the clinician's hands allowing the clinician to isolate adhesions and restrictions, and treat them very precisely. The promoters also claim that the metal surface of the instruments do not compress the tissues, as do the fat pads of the finger, so that deeper restrictions can be accessed and treated. However, we are not aware of any high level evidence to support any of these claims. There are six numbered instruments of different shapes and sizes designed for different areas of the body.

At present, limited research has been undertaken to determine the effectiveness of GT. Only one pilot study exists in which two manual therapy techniques were utilised: Graston instrumented soft tissue mobilisation and soft tissue mobilisation administered by the clinician's hands in the treatment of carpal tunnel syndrome [5]. While no differences were observed between the two manual therapies, both showed improvements in nerve conduction latencies, wrist strength and wrist motion. These improvements were maintained at 3 months follow up. There was no comparison with a placebo or sham treatment.

In terms of spinal musculature, one case study has been published in the treatment of sub-acute lumbar compartment syndrome with Graston Technique [6]. Following 6 treatments, the patient experienced a full resolution of the complaint and fascial extensibility was restored.

Given the overall lack of scientific evidence it is apparent that further high quality trials are necessary to determine the efficacy of the soft tissue massage method known as Graston Technique and SMT. We propose a study to determine the efficacy of SMT compared to Graston Technique in the treatment of non specific thoracic pain.

## Methods and design

This study will be a randomised, placebo-controlled trial comparing two different treatment modalities to an intervention of no known benefit for people with acute or sub-acute thoracic spine pain. The therapy arms will consist of SMT and Graston Technique (GT) and the placebo will be non-functional ultrasound. A placebo group will be utilised because at present there are no proven treatments for non specific thoracic pain. Reporting of this trial will adhere to the CONSORT statement [7-9] and is registered with the Australia and New Zealand Clinical Trials Registry [10]. Ethics approval has been granted by Murdoch University Human Research and Ethics Committee, number 2007/274.

The aim of this three arm trial is to test the efficacy of SMT and GT as independent modalities compared to detuned ultrasound for the outcomes of pain and disability measured using the Visual analogue scale (VAS) and a modified Oswestry Back Pain Disability Index.

### Study sample and participant enrolment

The study will be conducted at the Murdoch University Chiropractic student clinic in Perth, Australia. Participants will be recruited by the use of advertisements posted around the Murdoch University Campus, on local community boards and in newspapers. Any person who responds to the advertisement with symptoms consistent with non-specific thoracic spine pain and meets the inclusion criteria in the screening checklist via phone interview will be considered a potential participant for the study. Participants will be at least 18 years old with a primary complaint of thoracic pain (Figure 1: Mannequin defining the area of thoracic pain) and with no contraindications to manual therapy or Graston Technique.

**Figure 1 F1:**
[figure not shown]
Definition of thoracic spine pain area.

Upon making an appointment at the Murdoch University Chiropractic Clinic subjects will be screened and investigated with a detailed history and physical examination by Research Assistant A (a trained final year chiropractic student). The potential patients will be considered suitable candidates for the study if they meet all the inclusion criteria and none of the exclusion criteria are found. At this point, participants who agree to enter the trial will read and sign an informed consent form that will be administered and witnessed by Research Assistant A. All persons who enter the trial will be properly accounted for and attributed at the conclusion of the trial. Refer to Figure 2 for a flow diagram of the methods.

**Figure 2 F2:**
[figure not shown]
Flow chart of study.

### Inclusion Criteria

People will be included into the trial if they meet the following criteria:

1. Age 18 years or older with non-specific thoracic spine pain, which is pain in the region from T1 to T12 (Figure 1) and complies with the descriptive classification by Triano et al [11] (Table 1). For the purpose of this trial our definition will include an area outside the midline.

**Table 1 T1:** Definition of non specific Thoracic spine pain [11]

**Definition of non specific Thoracic spine pain**
Midline back pain – for the purposes of this trial, the pain will be bound by the lateral margins of the thorax laterally and the trapezium superiorly
Non dermatomal referred pain difficult to localise
No signs of nerve root tension
No major neurological deficit
Pain with compression over the thoracic spine into spine extension
Reduced range of motion

2. A VAS score of 2 out of 10 [12] or greater and an Oswestry Back Pain Disability index score of greater than 15% at baseline [13].

### Exclusion Criteria

People will be excluded if they meet any of the following exclusion criteria:

1. Have a contraindication to manual therapy (inclusive of osteoporosis, thoracic fracture, spinal infection, neoplastic disorders, spondyloarthropathy, clinical examination suggestive of frank disc herniation or generalised infection such as influenza).

2. Have contraindications to Graston technique (inclusive of neoplastic disorders, kidney infection, anticoagulant medication, rheumatoid arthritis, uncontrolled hypertension, thoracic fracture, osteomyelitis or generalised infection)

3. Have somatic conditions found on examination to refer pain to the thoracic spine from outside the defined area (inclusive of cervical zygapophyseal joints, muscles and discs)

4. Have an active history of visceral conditions referring pain to the thoracic spine (inclusive of myocardial ischaemia, dissecting thoracic aortic aneurysm, peptic ulcer, acute cholecystitis, pancreatitis, renal colic, acute pyelonephritis)

5. Have a current substance abuse problem.

6. Are not fluent and/or literate in the English language

7. Are currently receiving care for thoracic pain from any other provider

8. Cannot commit to the full study protocol

9. Are currently seeking compensation or have commenced litigation for thoracic spine pain

Radiographs will be taken when deemed necessary to exclude patients with contraindications to manipulation or other complicating disease, as described in the exclusion criteria. The decision to use x-ray will be based on the criteria set by the National Health and Medical Research Council for acute thoracic pain [14].

### Treatment allocation

Randomisation will occur directly after baseline measures are undertaken and after the subject has been screened for inclusion and the history, physical examination, report of findings and consent has been completed. An online randomisation site, Research Randomiser [15], will be used to generate treatment allocation. This online randomisation module is a web browser application that supports online randomisation of patients into healthcare trials. Research Randomizer uses the "Math.random" method within the JavaScript programming language to generate its random numbers. To prevent delay in the processing of participants, 100 random sequences will be generated, and then the sequences will be placed in sequentially numbered, opaque, sealed envelopes and stored in a sealed box. As each participant enters the trial the next consecutive opaque, sealed envelope will be given to the treating student and supervising clinician by Research Assistant A. This will allocate the treatment the participant is due to receive. Allocation is kept secure and concealed in the envelope until the patient information has been entered and the person requesting the randomisation has confirmed that they wish to proceed with entry into the trial. The participants will be analysed in the groups to which they are randomised using intention to treat analysis.

### Interventions and treatment

Participants will be randomised to one of three treatment arms as follows:

1. Chiropractic group: a series of chiropractic manual adjustments (SMT) to the thoracic spine administered by a registered chiropractor or a final year chiropractic student under the direct supervision of a registered chiropractor.

2. Graston Technique group: Graston Technique will be administered by final year chiropractic students who have been certified in module one of the Graston Technique, under the direct supervision of a registered chiropractor who will attend each consultation and place their hands on the anatomical regions involved;

3. Placebo group: participants will receive a session of de-tuned ultrasound administered by a final year chiropractic student, under the direct supervision of a registered chiropractor who will attend each consultation and place their hands on the anatomical regions involved.

All treating students will be trained to show the same enthusiasm for all three treatment modalities. The time taken for each consultation for the three treatment modalities will be approximately the same and last about 10 – 15 minutes. In the group that receives SMT, the spinal level(s) selected for SMT will be at the discretion of the student using usual chiropractic diagnostic methods including both motion and static palpation (application of pressure to tolerance directly over the facet joints) [16]. The SMT itself consists of taking the joint slack to the elastic barrier and a high-velocity low-amplitude thrust delivered at the level, and in the direction, of the notional loss of joint motion (fixation). Low velocity techniques and mobilisation will not be considered as manipulation for the purposes of this protocol. The SMT will be considered to be successful if the registered chiropractor who is supervising the final year student is satisfied with the administration and delivery of the manipulation itself. The participants will receive a maximum of 10 sessions of manipulation over a minimum period of 3 weeks to a maximum period of 4 weeks with 3 to 4 sessions per week. This dosage of treatment is based on the randomised controlled trial undertaken by Haas et al [17] who concluded that relief in low back pain intensity and functional disability was most substantial in those patients who received chiropractic treatment 3 to 4 times per week for 3 weeks.

The participants allocated to the Graston Technique Protocol will receive treatment as required to thoracic spine musculature inclusive of the Rhomboids Major and Minor, Upper and Lower Trapezius, Latissimus Dorsi and Levator Scapulae. The Graston Technique treatment will be administered by students who have successfully completed a Level 1 Graston training program and will involve the use of the patented form of instrumented-assisted soft tissue massage/mobilisation. The treating student will initially scan the area for notional "muscle adhesions" using the Graston instruments. Once the tissue area of interest has been localised instruments three and six will be utilised to apply deeper pressure for approximately 1 to 2 minutes to the area of concern. The participants will be scheduled to receive 10 treatments over a period of 3 to 4 weeks complying with that recommended by the developers of the technique [4].

The placebo group will be given eight minutes of detuned ultrasound for up to 10 sessions over a 3 to 4 week period. This control modality will be used as there is no known treatment benefit from the detuned machine; however, it has been established in previous trials that participants view this as a credible treatment option [18,19]. To increase the perceived credibility, the treating student will place one hand on area adjacent to the participants' involved mid-back region while delivering the treatment. The participants will be treated with the same enthusiasm as other treatment groups. Participants in this group will also undergo an examination including routine screening for contraindications at the first consultation and the normal clinical reassessment that would occur at subsequent treatments as per the intervention groups. Each placebo treatment session will be about 10–15 minutes in duration to match the active treatment sessions. Following the review period of 12 months, participants in this group will be offered the treatment of their choice (SMT or GT).

Participants will be monitored to ascertain whether their pain levels have increased beyond their baseline measurement or reduced to no pain at all. In such cases, the participants who cease to receive treatment due to an increase in pain will be noted and followed up. This occurrence will also be noted under adverse effects. On the other hand those who recover completely will be noted as a success. All participants will be followed up over the 12 months.

### Outcome measures and baseline data

Socio-demographic and other possible prognostic factors will be collected at baseline. Socio-demographic variables include age, sex, race/ethnicity, education, household income, marital status, and current employment status. General health status will be measured at baseline with the 36-item Short-Form Health Survey (SF-36) which has 8 scales: physical function, role physical, bodily pain, general health, vitality, and social function, role emotional and mental health. These can be aggregated into two summary measures: physical and mental health. Questions regarding previous episodes of thoracic pain and number of episodes in the last 2 years will be asked in the initial screening questionnaire.

Two main self assessment outcome measures will be used in this study; a 100 mm VAS for the participant's perception of pain intensity and a modified Oswestry Back Pain Disability Index to measure the participant's perceived disability and function.

The VAS is a tested and established instrument for the assessment of pain [20,21]. It consists of a horizontal line 10 cm long with the words "no pain" at one end and "pain as bad as it could be" at the other. Participants are asked to indicate which point along the line best represents their pain intensity. The distance from the no-pain end to the mark made by the participant is their pain intensity score. The Oswestry Back Pain Disability Index (ODI) has also been validated for the low back [22,23] and consists of 10 items assessing the level of pain interference with physical activities (e.g. pain intensity, lifting and travelling) resulting in a disability percentage. If some single items are not answered, the overall score is computed from the available information. For the purpose of this study, the Oswestry Back Pain Disability Index will be modified slightly, changing the words 'leg pain' to read 'back pain as seen in the diagram provided'. We acknowledge that with this change we cannot make the assumption that the instrument is reliable and valid for pain and disability in the thoracic spine. However it is likely on the face of it that the instrument is transferable from low back to mid back application.

Main outcome measures (VAS and ODI) will be taken at baseline, one week after treatment commences, upon completion of the 4-week intervention period and at three, six and 12 months post randomisation. Outcome assessments completed on the day of randomisation will be given to an independent research assistant B (not involved in treatment delivery) and placed in a secure box to be assessed only by the research co-ordinator. A statistician blinded to group allocation will analyse the data. At the first consultation a package will be given to the participants with the remaining five assessments to be completed on the dates advised in the package. A text message will be sent to the participant on the day that the outcome is due to be completed as a reminder to fill it out and return it back to the student clinic via a stamped envelope contained in the package. If the outcomes are not returned in a timely manner, an additional copy of the outcome measures will be sent to participants encouraging them to complete the forms.

### Adverse Effects

Participants will be provided with a list of potential adverse effects in an information letter prior to giving to consent. Information about adverse events and side effects will be collected in the form of a log book which will be handed to the participants in a package following their initial consultation. This will allow the participant to note any adverse effects, how long it lasted, a pain rating out of 10 and how often it occurred. Participants responses to the question of adverse effects will be collected at the six month follow up stage. At six and twelve months we will also collect data from the log books on additional treatment received for their mid back pain after the treatment intervention period.

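### The adverse-effect log, as described, has pain as its only intensity item and no onset date, so non-painful effects go ungraded and on-treatment effects cannot be separated from later ones

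*Protocol article*

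**What the plan says.** The Adverse Effects section names the instrument: "Information about adverse events and side effects will be collected in the form of a log book". Participants receive it in a package after the initial consultation and can use it to "note any adverse effects, how long it lasted, a pain rating out of 10 and how often it occurred". On timing, the section says "Participants responses to the question of adverse effects will be collected at the six month follow up stage". The same log books also supply data, at six and twelve months, on "additional treatment received for their mid back pain after the treatment intervention period".

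The abstract gives the length of treatment: "Each group will receive up to 10 supervised treatment sessions at the Murdoch University Chiropractic student clinic over a 4-week period". The Interventions and treatment section puts it at 3 to 4 weeks.

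That section also gives the one other stated route by which an adverse effect enters the record. Pain is monitored against baseline, and for a participant who stops treatment because pain has increased, "This occurrence will also be noted under adverse effects".

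**The concern.** Two properties of the listed fields limit what a harms table could show.

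**Severity.** The only intensity item is a pain score. Some effects that matter for manual therapy or instrument-assisted massage need not hurt, such as bruising or numbness. The article's own contraindications point to mechanisms beyond pain. Those for Graston Technique include "kidney infection, anticoagulant medication, rheumatoid arthritis, uncontrolled hypertension, thoracic fracture", and those for manual therapy include osteoporosis and suspected frank disc herniation. For a non-painful effect, the described log gives presence, duration and frequency, but nothing on how bad it was.

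**Timing.** Duration and frequency do not give an onset. Treatment is short, the stated collection point is much later, and the article provides for recording other treatment in between. If entries were undated, an effect of outside care could be tabulated against the randomised arm, and an effect arising in the treatment weeks could not be picked out.

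At stake is how the safety comparison of the two active arms with detuned ultrasound can be read. An analysis plan cannot repair this later, because it cannot recover an onset date or severity grade that was never written down.

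**Working it through.** The article attaches no sample size, rate or error level to adverse effects, so there is no stated figure to reproduce. The check is mainly a comparison of sections.

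**Step 1: what each listed field can answer.**

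| Field in the log | Did it occur? | How severe, if not painful? | When did it start? |
|---|---|---|---|
| The effect itself | yes | no | no |
| Duration | – | no | no |
| Pain rating out of 10 | – | no (painful effects only) | no |
| How often it occurred | – | no | no |

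Occurrence is covered. Severity of a non-painful effect and time of onset are not covered by any listed field.

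**Step 2: whether another stated route fills the gaps.** Stopping treatment because of increased pain is an on-treatment event by nature, so its timing is roughly known. It is triggered by pain alone, however, so it adds nothing for non-painful effects, and it misses events that did not end treatment. Routine clinical reassessment at treatment visits is mentioned, but the article does not say that adverse effects are recorded from it.

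**Step 3: the gap between treatment and collection.** Inputs: treatment of 3 to 4 weeks (Interventions and treatment) and collection at six months (Adverse Effects). Six months less about one month of treatment leaves about five months between the end of treatment and the stated collection.

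**Step 4: scale, under an assumption.** Suppose the responses cover the whole time from randomisation to six months, about 26 weeks. The article does not say this.

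- With 4 weeks of treatment: 4/26 = 15% on treatment, and (26 − 4)/26 = 22/26 = 85% after it.
- With 3 weeks of treatment: 3/26 = 12% on treatment, and 23/26 = 88% after it.

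These are shares of time, not of events. Treatment-related effects may well cluster in the treatment weeks, so the figures do not estimate how many events would be misplaced. They show only that most of the window would lie outside treatment, which is why an onset date is worth having.

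**Step 5: whether outside treatment falls in that window.** The article plans for it: "At six and twelve months we will also collect data from the log books on additional treatment received". It does not say how common such treatment will be. Placebo participants are offered an active treatment of their choice only after the 12-month review, so any such care before then would come from outside the trial.

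**The case against.** The strongest objection is that one summary sentence in a journal article is being read as the complete form. The article says what the log lets participants note. It does not say the list is exhaustive or that entries are undated, and articles commonly leave form fields to the full document. The same log books must also identify treatment received after the intervention period, which suggests that some timing is recorded. This stands as a limit on the point: the form may already carry dates, and the conclusion applies only to the fields listed. It does not remove the point, because the article chose to list the fields, and following that list exactly would leave both gaps.

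Three stronger readings are tempting, and the article does not support them.

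- *Non-painful harms would score zero or disappear.* The log takes any adverse effect, so a bruised or numb participant still produces a described, countable event. No rule is stated that grades events by the pain rating or compares arms on it.
- *The gaps push the arms together and make the active treatments look as safe as placebo.* That would need event rates, rates of outside treatment and a comparison rule, and none is given. Counts of events by arm do not depend on the pain rating.
- *The contraindications show which harms to expect.* People with those conditions are excluded. The list indicates kinds of harm a pain score does not grade, but says nothing about their frequency in this trial.

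It is also fair to say that the order of harms analyses belongs in an analysis plan. What the log collects does not: it is handed out after the first consultation, so its fields have to be settled before then.

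**Conclusion.** The point holds in a limited form. As described, the log has pain as its only intensity item and lists no onset date or session link, and adverse-effect responses have one stated collection about five months after treatment ends. From those fields, non-painful effects can be counted but not graded, and effects arising in treatment cannot be told from later ones.

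The size and direction of any effect on the comparison between arms are unknown. The conclusion assumes that the form holds no more than the fields listed; if it already has a start date and a severity item not based on pain, the point falls away. The 15%/85% split further assumes a 26-week record and describes time only.

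This is a low-priority improvement. The trial's primary question concerns pain and disability, but the change is cheap and the missing information could not be recovered reliably afterwards.

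**What to change.** Check the log form. If they are not already there, add two items per event:

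1. a start date;
2. a severity item not based on pain, for example mild, moderate or severe according to interference with usual activities.

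Keep the pain rating for painful events. In the report, tabulate events with onset in the treatment period by arm, and show later events separately, alongside additional treatment received.

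The cost is two extra columns in a log book that is already handed out, and a slightly longer entry for each event. Because participants hold the log from the first consultation, a start date can be written when the event happens and need not be recalled at six months. If logs are already in use, revised pages can be issued, and the report should say which entries lack the new items.

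### Apart from treatment stops for increased pain, participant-reported adverse effects have no stated collection before six months, and other care during weeks 0–4 is not recorded

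*Protocol article*

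**What the plan says.** All places are in the protocol article.

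- **Treatment period** (Abstract, Methods): "Each group will receive up to 10 supervised treatment sessions at the Murdoch University Chiropractic student clinic over a 4-week period".
- **Recording of harms** (Adverse Effects): "Information about adverse events and side effects will be collected in the form of a log book which will be handed to the participants" after the initial consultation. Its purpose is stated: "This will allow the participant to note any adverse effects, how long it lasted, a pain rating out of 10 and how often it occurred".
- **Retrieval of harms** (Adverse Effects): "Participants responses to the question of adverse effects will be collected at the six month follow up stage".
- **Other care** (Adverse Effects): at six and twelve months the log books also supply data on "additional treatment received for their mid back pain after the treatment intervention period".
- **Second harms record** (Interventions and treatment): "Participants will be monitored to ascertain whether their pain levels have increased beyond their baseline measurement or reduced to no pain at all". Participants who stop treatment because pain has increased are noted and followed up, and "This occurrence will also be noted under adverse effects".
- **Existing postal returns** (Outcome measures and baseline data): "At the first consultation a package will be given to the participants with the remaining five assessments". These fall at one week, four weeks, and three, six and twelve months. A text message goes out on each due date, and a second copy of the outcome measures is mailed if a form is late.

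**The concern.** The effects of most interest arise during or soon after the treatment sessions, yet the participant's account of them is stated to come in about five months later. It then depends on the participant still having the log book and still responding. A participant who reacted badly may be less likely to do either. If so, the missing logs are not a random sample, and the adverse-effect rate in each arm comes out too low. If the pattern differs between arms, the comparison of arms is distorted as well.

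The second gap concerns other care. Someone who sought treatment elsewhere in the first four weeks would not show up in data limited to the time after the intervention period. Pain and disability are compared between arms at one and four weeks, so other care used unequally in that window could affect those results without being visible.

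**Working it through.** The article gives no dropout rate, no adverse-effect rate and no harms precision target, so there is no figure of its own to reproduce. The check is a timeline, a comparison of the stated records, and an illustration under assumed rates.

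**1. Gap.** Treatment ends by week 4. Six months is about 26 weeks. 26 − 4 = 22 weeks.

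**2. What the article states is collected, and when.**

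| Time | Pain and disability form | Adverse-effect question or log | Other care |
|---|---|---|---|
| During treatment | – | Only stops for increased pain | None stated |
| 1 week | Yes | None stated | None stated |
| 4 weeks | Yes | None stated | None stated |
| 3 months | Yes | None stated | None stated |
| 6 months | Yes | Yes | Yes, for care after the intervention period |
| 12 months | Yes | None stated | Yes, for care after the intervention period |

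Three postal returns precede the first one for which adverse-effect collection is stated. The mailing of a second copy is stated for the outcome measures; the log book is not mentioned there.

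**3. What the second record covers.** It covers increased pain that leads to a stop of treatment. An effect of another kind, or increased pain that did not stop treatment, has no stated adverse-effect record before six months.

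**4. Loss unrelated to harm (assumed rates).** Take 28 per arm (84 / 3, from the Abstract), an assumed 10% event rate and 10–30% non-response at six months.

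- Expected events per arm: 28 × 0.10 = 2.8.
- Events lost per arm: 2.8 × 0.10 = 0.28 to 2.8 × 0.30 = 0.84.
- Upper 95% limit on the risk of an effect never seen, 1 − 0.05^(1/k): 10.1% with k = 28, 11.3% with k = 25 (10% lost), 13.9% with k = 20 (30% lost).

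With 30 per group, as in Sample size calculations, the limits are 9.5% (k = 30), 10.5% (k = 27) and 13.3% (k = 21). Loss of this kind costs some precision and does not bias the rate.

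**5. Loss related to harm (assumed rates).** Let r be the true risk, dA the loss among those with an effect, and d0 = 0.10 the loss among the others. Then

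observed risk = r(1 − dA) / [r(1 − dA) + (1 − r)(1 − d0)].

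For r = 0.20 and dA = 0.40: 0.12 / (0.12 + 0.72) = 14.3%.

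| True risk | dA = 10% | dA = 20% | dA = 40% |
|---|---|---|---|
| 10% | 10.0% | 9.0% | 6.9% |
| 20% | 20.0% | 18.2% | 14.3% |
| 30% | 30.0% | 27.6% | 22.2% |

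Even with the same loss pattern in both arms (dA = 40%), a true difference of 30% − 10% = 20 points would appear as 22.2% − 6.9% = 15.3 points.

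**6. Other care.** Exclusion criterion 7 removes people already under another provider's care for thoracic pain at entry. Nothing in the article records such care if it starts during weeks 0–4. Data analysis compares the primary outcomes at one and four weeks.

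**The case against.** The strongest reply is that harms are not invisible during treatment. Participants attend supervised sessions with clinical reassessment, pain is monitored, and stops for increased pain are entered as adverse effects. The pain and disability forms due back at one and four weeks would also show worsening. This stands, so a reader who infers that nothing about harms is known before six months goes further than the article allows. It does not close the gap, because no adverse-effect question is stated for the visits or the early forms.

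The log book is also meant to be filled in at the time, so recall matters only where it was not kept. That stands: the delay is in retrieval.

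A reader might infer that data are lost for everyone who drops out. Stopping treatment is not leaving follow-up: the article intends to follow all participants for 12 months. The log books are used again at twelve months, although only additional treatment is named there. The supported statement is that logs of people who stop responding earlier are probably lost.

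A reader might also infer that ordinary non-response would remove one or two of about three events per arm. The arithmetic does not support this. Losing one or two of 2.8 needs 1 / 2.8 = 36% to 2 / 2.8 = 71% loss among those with an event. With so few events the comparison of harms would be imprecise even if complete, and Data analysis names no test of harms between arms.

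On other care, exclusion criterion 7 limits its use at entry. It does not measure what starts later.

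Finally, this is a condensed article. Reporting of serious events may be set out in the full protocol, and its absence here is not counted against the plan.

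**Conclusion.** The point holds in a limited form. The article fixes six months as the only stated collection point for the adverse-effect question and log, about 22 weeks after treatment ends, with stops for increased pain as the one exception. This is a stated choice, not a detail left to another document. Loss unrelated to harm costs a little precision. Loss related to harm lowers the observed rates, by an amount the article does not allow anyone to estimate; the figures above rest on assumed risks and losses and show direction and a possible range only.

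The gap in other care during weeks 0–4 is also real as stated. Its effect on the one-week and four-week results cannot be sized from the article. Neither gap undermines the trial's main comparisons; both call for an inexpensive improvement in data collection.

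**What to change.** - Add the adverse-effect question, or a page of the log, to the one-week and four-week forms already in the participant's package. Extend the reminder and second-copy procedure to it.
- Add a question on other care for mid back pain to the same two forms, covering the time since randomisation.
- Keep the six-month question for late effects.
- Describe the log book and the record of stops for increased pain in one place, so that it is clear how the two are combined in the harms report. This concerns data collection only; no change to treatment or stopping is proposed.

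The cost is about one extra page in two existing forms and slightly more burden for participants.
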